## Abstract

Fear of falling is a prevalent and disabling problem after stroke, contributing to reduced activity, impaired balance, and increased fall risk. Recent studies indicate that virtual reality (VR)–based interventions and transcranial direct current stimulation (tDCS) applied during exercise therapy may help reduce fear of falling in individuals with neurological disorders.

This single‑center, assessor‑blinded randomized controlled trial aims to compare the effects of VR‑based gait training with tDCS combined with gait training on fear of falling in patients with subacute stroke. Participants will be randomly allocated to either the VR or tDCS group, while all also receive conventional physiotherapy. Outcomes will be assessed at baseline and after ten treatment sessions by a blinded assessor. The primary outcome is fear of falling, measured using the Falls Efficacy Scale‑International (FES‑I). Secondary outcomes include balance, assessed by the Mini‑BESTest and Biodex Balance System, as well as walking ability, assessed by the 10‑Meter Walk Test. It is hypothesized that VR‑based gait training will result in a greater reduction in fear of falling than tDCS combined with gait training.

Specifications table

**Table utbl0001:** 

**Subject area**	Neuroscience
**More specific subject area**	*Fear of falling*
**Name of your protocol**	*Comparing the effect of virtual reality and transcranial direct current stimulation on fear of falling, balance, and walking ability in patients with stroke*
**Reagents/tools**	• The Falls Efficacy Scale International questionnaire • The shortened version of the Balance Evaluation Systems Test • The Biodex Balance System • The 10-Meter Walk Test
**Experimental design**	*Stroke patients will be allocated to two intervention groups, Virtual Reality and transcranial Direct Current Stimulation combined with gait training . All participants will receive conventional physiotherapy also. Group allocation will be performed using block randomization stratified by sex and history of falls. The outcome measures include fear of falling, balance, and walking ability. These variables will be assessed at prior to the initiation of treatment and the day after the last session.*
**Trial registration**	*Registration No.: IRCT20251005067515N1*
**Ethics**	• The study will be conducted in accordance with the Declaration of Helsinki and approved by the Ethics Committee of the University of Social Welfare and Rehabilitation Sciences (IR.USWR.REC.1404.126). • Written informed consent will be obtained, and participants will be informed of study procedures, confidentiality, and their right to withdraw at any time.
**Value of the Protocol**	• To compare the effects of virtual reality versus tDCS during walking on fear of falling in stroke patients. • To evaluate the potential of technology‑assisted rehabilitation to enhance post‑stroke recovery. • To provide clinical evidence on the applicability and effectiveness of VR‑ and tDCS‑based interventions in routine stroke rehabilitation.

## Background

Stroke remains one of the most significant public health challenges, ranking as the second cause of death in older adults and fifth among younger populations. Annually, about 15 million people suffer a stroke, leading to millions of deaths and long-term disabilities [1].

Falling represents significant barrier to functional recovery and community reintegration in individuals who have sustained a stroke. Research findings on predictors of falls indicate that fear of falling is the third most important contributor to falls in stroke patients, following physical impairments in balance control and muscle strength during walking [2,3]. This fear can initiate a detrimental cycle: the ‘vicious cycle of falling’, where fear leads to reduced activity, which in turn impairs balance, increasing the likelihood of falls. These falls then intensify the initial fear, perpetuating a cycle that hinders effective post-stroke rehabilitation [4]. Consequently, Fear of falling is regarded as a psychological–cognitive factor rather than merely a consequence, underscoring the importance of early identification and timely intervention to disrupt this maladaptive cycle [5]. Recognizing the limitations of conventional gait training alone for achieving higher-level recovery in stroke patients, recent systematic reviews advocate for combined and innovative exercise approaches [6].

Among these, Virtual Reality (VR) technology allows for the creation of ecologically valid, yet controlled, environments that challenge postural control and gait parameters. VR platforms provide immediate, quantifiable, and personalized visual feedback regarding performance metrics such as step length variability, gait symmetry, and deviation from a target path[7]. Several studies have reported the beneficial effects of virtual reality on older adults, balance in patients with stroke, and reduction of fear of falling in patients with Parkinson’s disease and multiple sclerosis [[8], [9], [10], [11]]. This intensive, repetitive practice, coupled with extrinsic feedback, is hypothesized to drive neuroplastic changes facilitating improved motor learning and, consequently, reduced FoF^1^ and enhanced balance [12].

Another promising intervention is Transcranial Direct Current Stimulation (tDCS), a non-invasive technique that modulates cortical excitability using weak electrical currents. Targeting the dorsolateral prefrontal cortex (DLPFC) is relevant as this area is heavily implicated in cognitive control, executive function, planning, and the regulation of movement and fear/anxiety responses [13,14]. Several studies have shown that tDCS improves balance and gait parameters in older adults and individuals with stroke [[15], [16], [17]]. Moreover, tDCS is currently being used as a recognized guideline-based intervention for reducing fear and stress [18,19]. By employing anodal stimulation over the DLPFC during active motor tasks (walking), we aim to enhance cortical excitability in relevant motor networks, potentially augmenting the benefits derived from the concurrent physical training and promoting more robust motor relearning and confidence building [15,20].

This randomized controlled trial compares virtual reality and tDCS‑assisted walking. hypothesizing that VR, through real‑time multisensory stimulation and engagement of the mirror neuron system, produces greater effects than tDCS, which primarily targets central nervous system–mediated stress reduction and neuroplasticity.

## Description of protocol

### Study design

This study is a single-center, assessor- and analyzer-blinded, parallel-group randomized controlled trial comparing two high-intensity rehabilitation approaches: VR-based gait training and tDCS applied concurrently with parallel-bar gait training. The trial will be conducted at Rofeideh Hospital, affiliated with the University of Rehabilitation Sciences and Social Health, Tehran, Iran, where all intervention sessions and outcome assessments will take place (Table 1).

**Table 1 tbl0001:** Participant flow of enrolment, assessments and interventions.

	T0	T1	TT	T2
*Recruitment*	***			
*Interview (inclusion/exclusion)*	***			
*Assigning Consent form*		***		
*Randomization*		***		
*Questionnaires (HADS; MMSE; FES-I; Mini-BEST; 10MWT)*		***		***
*Assessment of balance (Biodex balance system)*		***		***
*VR, tDCS training intervention*			***	

T0, prior to study; T1, baseline (pre-intervention); TT, training time; T2, post-intervention test. HADS, Hospital Anxiety and Depression Scale; MMSE, Mini-Mental Scale Examination; FES-I, Falls Efficacy Scale International; Mini-BEST, shortened version of the BESTest, 10MWT; 10‑Meter Walk Test.

### Inclusion and exclusion criteria

32 stroke patients will be recruited for this study. inclusion criteria: Age between 40 and 70 years [21]. 2. Confirmed diagnosis of unilateral ischemic stroke in the subacute phase (3–6 months post-onset) [6] 3. Ability to walk independently for a minimum of 10 m, potentially with the assistance of a single standard walking aid [22]. 4. Hospital Anxiety and Depression Scale (HADS) score < 16 to ensure participants’ ability to cooperate and to exclude cases of severe depression [23]. 5. Cognitive screening score ≥ 21 on the Mini-Mental State Examination (MMSE) [24]. 6. Spasticity severity of the ankle dorsiflexor group, according to the Modified Ashworth Scale (MAS), on the injured side 2 or less [25]. Exclusion Criteria: 1. Significant orthopedic, vestibular, or cardiovascular conditions precluding safe gait training. 2. Presence of implanted metallic devices, pacemakers, deep brain stimulators. 3. Presence of major neurological comorbidities or psychiatric disorders. Participant recruitment will take place through the inpatient neurological rehabilitation wards of Rofeideh Hospital and affiliated units of URSSH. Throughout all treatment sessions, if the participant experiences severe fatigue, blurred vision, dizziness, or any other unexpected adverse sensation, the intervention will be immediately discontinued. The trial will also be stopped for any participant who shows sensitivity or intolerance to tDCS, expresses unwillingness to continue participation, or develops any of the exclusion criteria during the study period.

A blinded assessor will evaluate outcomes at baseline and after ten physiotherapy sessions, with assessments scheduled to avoid unblinding. The study follows the Declaration of Helsinki, written informed consent will be obtained, and participants’ demographic and clinical information will be recorded after randomization.

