### Random allocation

participants will be randomly assigned in a 1:1 ratio to either the VR-based rehabilitation group or the tDCS group. Block randomization will be performed, stratified by sex and history of falling (presence or absence of previous falls). A computer-generated randomization sequence will be created by an independent statistician, and allocation concealment will be ensured using sealed, opaque envelopes.

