#### VR‑based gait training group

Participants in the VR group will perform gait training on parallel bars using a virtual reality system. The VR system consisted of a Kinect 2 camera with a motion depth detection range of approximately 5 m, equipped with a moving depth path avatar extraction system. It provided real-time detection and feedback of lower limb joint angles in the sagittal plane, as well as stepping length feedback. VR‑based gait training is delivered in two 10‑minute phases. In the first phase, step length is adjusted using visual cues (green lines) on the VR screen based on the patient’s initial ability, and the patient practices forward and backward parallel walking accordingly (Fig. 1, step lenght). In the second phase, knee and ankle flexion range are adjusted using visual feedback on the screen (Fig. 2, knee and ankle flexion). Training is performed in an open environment, requiring the patient to focus on the VR instructions despite surrounding distractions. tDCS combined with gait training*:* tDCS combined with gait training receive transcranial direct current stimulation simultaneously while walking on the parallel bars for 20 min. The portable and lightweight tDCS device allows stimulation during gait training (Model: Segal Stim AT-12). (Fig. 3, tDCS device). The current intensity is set at 1- 1.5 mA (**as tolerated by the patient),** with the anodal electrode placed over either F3 or F4, depending on the side of the brain lesion, and the cathodal electrode positioned over the contralateral supraorbital area [26]. Typically, stimulation targets the dorsolateral prefrontal cortex (DLPFC), a region associated with the reduction of fear responses [27]. The F3 and F4 locations are identified based on the international 10–20 EEG electrode placement system.

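### The article ends the trial, not only the intervention, for participants who do not tolerate tDCS; only one arm can meet this ground, so randomised patients can be lost selectively

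*Protocol article*

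**What the plan says.** The section Inclusion and exclusion criteria has two stopping sentences, one after the other.

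- For severe fatigue, blurred vision, dizziness or another unexpected adverse sensation in any session, "the intervention will be immediately discontinued". This covers both arms and speaks of treatment.
- The next sentence speaks of the trial: "The trial will also be stopped for any participant who shows sensitivity or intolerance to tDCS, expresses unwillingness to continue participation". It adds a third ground, that the participant "develops any of the exclusion criteria during the study period".

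The two arms are described under the heading VR-based gait training group. For VR: "Participants in the VR group will perform gait training on parallel bars using a virtual reality system". The tDCS arm is to "receive transcranial direct current stimulation simultaneously while walking on the parallel bars for 20 min", with the current set "as tolerated by the patient". No stimulation is described for the VR arm.

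Under Random allocation, "participants will be randomly assigned in a 1:1 ratio". Table 1 puts randomisation at T1, before the training period.

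There is one assessment after baseline. The Abstract says: "Outcomes will be assessed at baseline and after ten treatment sessions by a blinded assessor". The section Inclusion and exclusion criteria also places it after ten sessions. The Specifications table instead places it on the day following the final session, and Table 1 calls T2 a post-intervention test. The article does not say what happens at T2 to a participant for whom the trial has been stopped.

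**The concern.** A randomised comparison is protected as long as the patients compared are those who were randomised. A rule that takes patients out after allocation, for a reason that one of the treatments causes and the other cannot, weakens that protection. Patients who do not tolerate stimulation may differ from those who do in anxiety, in expectation of benefit or in severity, and each of these could plausibly relate to fear of falling. If they leave without a T2 value, the tDCS mean describes those who tolerated it, while the VR mean faces no equivalent filter.

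This goes beyond missing detail. If the outcome is never collected, no later analysis plan can recover it, and labelling the analysis intention-to-treat does not create the value. The section Protocol validation says that recruitment and intervention are in progress, so the wording matters now.

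**Working it through.** **1. Which arm can meet which ground**

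| Ground | VR arm | tDCS arm | What is stopped |
|---|---|---|---|
| Fatigue, dizziness, other adverse sensation | yes | yes | intervention |
| Sensitivity or intolerance to tDCS | no | yes | trial |
| Unwilling to continue | yes | yes | trial |
| New exclusion criterion | yes | yes | trial |

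Only the second row is both trial-level and confined to one arm.

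**2. What happens at T2 for an early stopper**

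For a participant who completes treatment, the two statements of T2 timing agree. For one who stops early they do not. Read as after ten sessions, the visit never falls due. Read as the day after the final session, it could take place, but earlier in calendar time than for everyone else. If the trial has been stopped for that participant, neither statement clearly applies.

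**3. The plan's own sample size, for scale**

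Inputs from Sample size calculation: means 40.9 and 48.9 (difference 8.0), SDs 8.4 and 10.8, r = 0.6, alpha 0.05 (two-sided assumed), power 80%. With adjustment for baseline,

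n per arm = (8.4² + 10.8²) × (1 − 0.6²) × (1.96 + 0.84)² / 8² = 187.2 × 0.64 × 7.849 / 64 = 14.69, so 15 before dropout.

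With 15% dropout, 15 / 0.85 = 17.6, so 18. The stated 16 per group lies between the two. The present point does not depend on that gap; 16 is used below as the number randomised per arm.

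**4. Possible bias (illustration)**

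Let k of 16 tDCS patients be removed, and let their FES-I at T2 differ by D points from the mean of those retained. The mean of all 16 is then the retained mean plus kD/16. An analysis of retained patients only is therefore off by kD/16. Both k and D are assumptions, because the article gives neither.

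| k removed | D = 4 | D = 8 | D = 12 |
|---|---|---|---|
| 1 | 0.25 | 0.50 | 0.75 |
| 2 | 0.50 | 1.00 | 1.50 |
| 3 | 0.75 | 1.50 | 2.25 |
| 4 | 1.00 | 2.00 | 3.00 |

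The full range is 0.25 to 3.0 points, or 3% to 37.5% of the 8-point difference. Two removed with D of 4 to 8 gives 0.5 to 1.0 points (6% to 12.5%).

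Higher FES-I means more concern. If the removed patients would have scored higher, the bias favours tDCS; if lower, it favours VR.

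**5. Power**

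Power = Φ(8 / √[0.64 × (SD₁²/n₁ + SD₂²/n₂)] − 1.96).

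| Lost from the tDCS arm only | that arm has SD 10.8 | that arm has SD 8.4 |
|---|---|---|
| 0 | 83.2% | 83.2% |
| 1 | 81.7% | 82.3% |
| 2 | 80.0% | 81.3% |
| 3 | 78.0% | 80.1% |
| 4 | 75.8% | 78.7% |

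The largest drop is 83.2 − 75.8 = 7.4 percentage points. The main risk is bias, not power.

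**The case against.** The strongest reply is that too much is being read into a loosely edited article. The second stopping sentence follows straight on from the first, and the word *also* could mark it as a further list of reasons to stop treatment. The Specifications table ties T2 to the final session, and an early stopper has a final session too. Analysis set, missing data and follow-up after discontinuation are commonly left to a full protocol or analysis plan that is not shown.

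Part of this stands, and it rules out several stronger readings that a reader might infer:

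- **That early stoppers certainly have no T2 value.** The article is ambiguous here; it does not say they go unassessed.
- **That the plan specifies an analysis of completers only.** Data analysis names tests and software, not an analysis set. The bias table applies if the removed patients have no T2 value and only the others are analysed.
- **That the bias always favours tDCS.** Nothing in the article links intolerance to FES-I, so the direction depends on an assumption.
- **That 15% of the tDCS arm would be removed.** The 15% is one overall dropout allowance, with no cause and no split by arm. Setting the current to tolerance may keep intolerance rare.
- **That the whole stopping sentence is one-sided.** Unwillingness and new exclusion criteria apply to both arms, and losses from VR could offset or add to the bias.

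The bias may also be small relative to noise. With 16 per arm the standard error is √(0.64 × 187.2 / 16) = 2.74 points, so 0.5 to 1.0 points is 0.18 to 0.37 of a standard error.

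What the reply does not remove is the rule itself. Two adjacent sentences use different words, intervention and trial, and the second groups intolerance with unwillingness to continue participation. Site staff following it literally would end participation. That is stated text, not an omission left to another document.

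**Conclusion.** The point holds in a limited form. As written, the rule can remove randomised patients from the tDCS arm alone, for a treatment-related reason, with no stated provision for keeping them in follow-up. It can therefore bias the VR-tDCS contrast on the primary outcome.

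This rests on three things: that the word trial is meant literally, that only the tDCS arm is stimulated, and that nothing in the article places a T2 visit after participation has ended. Size and direction remain open. The 0.25 to 3.0 points is a what-if range for assumed values of k and D, not an estimate; the loss of power under the same assumptions is modest. The defect is worth correcting while the trial is running, but it does not by itself invalidate the design.

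**What to change.** 1. State that meeting the tDCS sensitivity or intolerance criterion ends the intervention and not trial participation.
2. In both arms, assess every randomised participant who has not withdrawn consent to follow-up at T2, at the calendar time to which the tenth session would have led.
3. Reconcile the T2 timing in the Specifications table with that in the Abstract and in Inclusion and exclusion criteria, so that it is defined for those who stop early.
4. State that participants are analysed in the group to which they were assigned, and report the number stopped and the reason by arm.

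When and why stimulation or training should be stopped is a clinical matter and is left as it is. The cost is a few sentences of text and the already planned T2 visit for the few participants who stop early.

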### Random allocation

participants will be randomly assigned in a 1:1 ratio to either the VR-based rehabilitation group or the tDCS group. Block randomization will be performed, stratified by sex and history of falling (presence or absence of previous falls). A computer-generated randomization sequence will be created by an independent statistician, and allocation concealment will be ensured using sealed, opaque envelopes.

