#### Data analysis

data normality will be assessed with the Shapiro–Wilk test. Depending on distribution, paired t‑tests or Wilcoxon tests will be applied for within‑group comparisons, and 2 × 2 repeated‑measures ANOVA will be used for between‑group analyses. Between-group differences were analyzed using ANCOVA, with time since stroke (post-onset duration) included as a covariate to account for potential differences in recovery status. Statistical analyses will be performed in SPSS v26, with significance set at p < 0.05.

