#### Sample size calculation

The primary outcome is fear of falling, measured by the FES‑I. As no MCID^2^ has been established for stroke patients, the MCID was estimated as 1.2 × the MDC (MDC^3^ = 6.69) based on previous studies [28,32].

Based on the standard deviation (SD) reported in the study by Molhemi et al. [9]., and according to the formula, sampsi 40.9 48.9, sd1(8.4) sd2(10.8) pre[1] post[1] r0(0.6) r1(0.6) alpha (0.05) power (0.8), assuming α = 0.05, power = 80%, and a pre–post correlation of 0.6, the calculated sample size was 16 participants per group, accounting for a 15% dropout rate [8,33].

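### Randomisation is stratified by sex and history of falls, but the ANCOVA omits both; if they are prognostic it is conservative, and adding them is a modest improvement at little cost

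*Protocol article*

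**What the plan says.** On allocation, the Random allocation section states "Block randomization will be performed, stratified by sex and history of falling", with 1:1 assignment to the two arms. The experimental-design row of the specifications table repeats the two factors.

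On analysis, the Data analysis section gives two between-group methods. One is a 2 × 2 repeated-measures ANOVA. The other is described as follows: "Between-group differences were analyzed using ANCOVA, with time since stroke (post-onset duration) included as a covariate". Neither method mentions sex or fall history.

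The sample size section gives its command as "sampsi 40.9 48.9, sd1(8.4) sd2(10.8) pre[1] post[1] r0(0.6) r1(0.6) alpha (0.05) power (0.8". It contains means, SDs and a pre–post correlation, and no term for stratification.

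The Background describes a cycle in which falls increase the fear that preceded them. That is the only support in the article for treating fall history as prognostic. It is qualitative, and nothing comparable is said about sex.

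**The concern.** Stratified blocks make the arms alike on sex and fall history, so those factors contribute little to the chance difference between arms. A model without them still counts their variance as residual error. When the factors are prognostic, the model's standard error is therefore larger than the true sampling error of the treatment estimate. Confidence intervals come out too wide, the test rejects too rarely under the null, and some power is forgone compared with a model that includes the factors.

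The article names a covariate that plays no part in the randomisation and leaves out the two that do. Because it names its covariate, this reads as a choice already made and not as a detail left open. With 32 patients, precision is worth keeping.

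**Working it through.** **Inputs from the article.** Difference 48.9 − 40.9 = 8.0; SDs 8.4 and 10.8; r = 0.6; alpha 0.05 (sidedness not stated, two-sided assumed); 16 per group; 2 × 2 = 4 strata.

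**Assumed, because the article gives no figure.** q, the share of FES-I variance explained by fall history: 0%, 10%, 20%. Blocks of 4 and four strata of 8 in the simulations.

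**1. The plan's own figure.** Pooled variance = (8.4² + 10.8²)/2 = (70.56 + 116.64)/2 = 93.6, so SD = 9.67. With baseline adjustment:

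n = 2 × 93.6 × (1 − 0.6²) × (1.960 + 0.842)² / 8² = 14.7, that is 15 per group before dropout.

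This is close to the stated 16. Allowing for 15% dropout gives 15/0.85 = 17.6, that is 18; that gap is a separate matter. What counts here is that nothing in the calculation relies on stratification.

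**2. ANCOVA as written (baseline FES-I not named).** Ignoring the factors, the standard error is about √(93.6 × 2/16) = 3.42. With strata balanced by design, the true standard error is about 3.42 × √(1 − q):

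- q = 10%: 3.42 × 0.949 = 3.24, so the unadjusted value is about 5% too large (1/√0.9 = 1.054).
- q = 20%: 3.42 × 0.894 = 3.06, about 12% too large (1/√0.8 = 1.118).

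Simulation with an 8-point effect, 32 patients, no dropout, and fall history acting equally on both FES-I measurements:

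| q | Power without factors | Power with factors | Type I error without factors |
|---|---|---|---|
| 0% | 61% | 60% | 4.8% |
| 10% | 61% | 64% | 4.1% |
| 20% | 61% | 71% | 3.3% |

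A separate simulation of the same setting gave power of 62% vs 66% at 10% and 61% vs 70% at 20%, with type I error of 4.0% and 2.8%. The pattern is stable to within about two points.

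**3. ANCOVA with baseline FES-I added.** Without the factor, the residual variance as a share of the total is 1 − 0.36 = 0.64. If fall history acts equally at both times and the overall r stays 0.6, the residual with the factor is (1 − q) − (0.6 − q)²/(1 − q):

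- q = 10%: 0.9 − 0.25/0.9 = 0.622, a reduction of 2.8%.
- q = 20%: 0.8 − 0.16/0.8 = 0.600, a reduction of 6.3%.

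Simulated power without vs with the factors was 79.2% vs 79.7% and 80.2% vs 81.9%; type I error without them was 4.8% and 4.4%.

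If instead fall history is unrelated to baseline but explains q of follow-up, it removes 0.10/0.64 = 16% or 0.20/0.64 = 31% of the residual. Power was then 81% vs 86% and 82% vs 91%, with type I error of 3.3% and 1.9% without the factors.

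**4. Group-by-time test of the repeated-measures ANOVA.** This is a comparison of change scores. With a time-constant factor, the variance of change is 2[(1 − q) − (0.6 − q)] = 0.8 of the total for any q, because the factor cancels. Simulated power was 70.8% vs 70.8% at 10% and 71.3% vs 71.1% at 20%.

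**The case against.** The strongest reply is that the loss depends on conditions the article does not establish. It gives no prognostic strength for either factor and no rationale for sex. If the factors are not prognostic, nothing is lost. That stands, and it is why the effect is given as a range starting at zero.

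Second, the article's own reasoning points to the smaller figures once baseline is in the model. If past falls have already raised fear, their effect is in the baseline FES-I, and adjusting for baseline absorbs most of it. A reader might infer a loss of 5 to 9 power points and a type I error near 2% whatever the model. With baseline included, those figures need fall history to predict follow-up FES-I beyond baseline, and nothing in the article supports that. This stands too.

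Third, a reader might infer that both between-group analyses suffer. The group-by-time test does not, unless the factors predict change.

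Fourth, no stated claim is broken: the 80% power took no credit for stratification, and the error is conservative, so it adds no false-positive risk. This stands.

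Fifth, the article is condensed, and a fuller plan could list more covariates. This carries less weight, because the article does name a covariate and it is neither of the two used for randomisation.

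The replies limit the size and reach of the point. None offers a reason to leave the factors out.

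**Conclusion.** The mismatch is real. Allocation uses sex and fall history; the ANCOVA as written adjusts for neither. Its direction is conservative and its size is conditional:

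- **ANCOVA as written:** about 3 power points forgone if fall history explains 10% of FES-I variance, about 10 if it explains 20%, and none at 0%.
- **With baseline FES-I in the model:** about 0 to 2 points, or about 5 to 9 if fall history predicts follow-up beyond baseline.
- **Group-by-time test:** no effect unless the factors predict change.

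These figures rest on the article's SDs, correlation and 8-point difference, on assumed values of q, on assumed block and stratum sizes, and on no dropout. The gap between the 61% baseline in these figures and the planned 80% comes from the ANCOVA not naming baseline FES-I, which is a different question from stratification.

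It would go too far to say that the standard error is too large, or that the benefit of stratifying is lost, as established facts. The documents support only the conditional statement. This is a modest improvement to efficiency and consistency, not a threat to the trial's validity.

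**What to change.** In the Data analysis section, add sex and history of falls as main effects to the ANCOVA for FES-I and to the corresponding models for the Mini-BESTest, Biodex and 10-Meter Walk Test outcomes.

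The cost is one phrase and two degrees of freedom (from 32 − 3 = 29 to 27 in the ANCOVA as written). Where the factors explain nothing, power moves by about one point (61% to 60%). The Protocol validation section says recruitment is under way and no outcome data have been generated, so the covariates can still be fixed before any results are seen.
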